### A.5 PARTICIPANTS

Please provide the following information on the participants with/from whom you expect to be collecting data:

#### A.5.1 Age/ Sex: (please enter the expected number in each of the boxes)

|         | Neonates
(<28 days) | Infants
(1-11 months) | Young children
(1-9 years) | Adolescents
(10-17 years) | Adults
(18 yrs & above) |
|---------|------------------------|--------------------------|-------------------------------|------------------------------|----------------------------|
| Males   |                        |                          |                               |                              |                            |
| Females |                        |                          |                               |                              | 1140                       |

*Guidance notes:-*

*This age/sex breakdown helps convey how vulnerable the participants will be*

*If you are unable to give precise figures, state estimates and give an explanatory sentence in the space below*

#### A.5.2 What specific measures are in place to take into account women of childbearing age?

*Guidance notes:*

*women may have different responses to disease processes*

*The developing foetus may be particularly vulnerable in intervention trials*

The study involves administration of a uterotonic agent (misoprostol or oxytocin) after the delivery of the baby. The drugs are not also known to circulate into the lactating milk nor do they pose a big risk to these women

#### A.5.3 Describe how and where the participants are to be recruited?

*Guidance notes:*

*This is distinct from the statistical sampling method described in A.4. You should outline the procedures for recruitment of each group of participants, include details on:*

- the setting (e.g. Country, Town, District, on the ward, out-patient department, in the home)*
- inclusion and exclusion criteria for selection, if relevant (e.g. "Women of child-bearing age will be excluded")*

The Randomized Controlled Trial (RCT) study will purposively be carried out in the Maternity ward of Mbarara Regional Referral Hospital (MRRH), rural south western Uganda which also doubles as a Mbarara University Teaching Hospital for the faculty of medicine. The hospital is located in Kamukuzi Division, Mbarara Municipality along 30° 20'E' and 31°20'E longitude and 1°30'S and 0°30'N Latitude (DISH, 2011 <http://www.ugandadish.org/>). The regional referral hospital receives mothers from different tribal and socio-demographic locations in Uganda. Though inadequate, the hospital is equipped with trained staff, midwives, and obstetricians able to offer emergency obstetric care (EMOC) facilities. The Hospital also has good blood transfusion services and theatre for additional therapeutic procedures that may be required to treat PPH. Mothers received in this hospital may therefore represent different mothers from various social and demographic backgrounds.

[figure not shown]

Mothers with IUFD, hypertensive disorders, cardiac or coronary disease, inflammatory bowel disease, elective or previous Caesarean Section, gestation age < 38 weeks of amenorrhea and hypersensitivity to prostaglandins will be excluded from this study due to their associated risks to PPH (Chien, 1999; Combs et al, 1991). Mothers will be consented during early stages of active labor (before 6 cms of cervical dilation) to give ample time for mothers to think through the consent process and avoid feeling coerced. The consented mothers will then be randomly assigned different treatment groups. These mothers will be blinded to the study group allocated.

#### **Intervention (COHORT) group**

The intervention group will be given sublingual misoprostol 600µg as part of the routinely done active management of third stage of labor within one minute of delivery. In this group, sublingual misoprostol 600µg will be administered as a prophylactic uterotonic agent. Delayed cord clamping will also be preferred due to documented benefits to the baby (Farrar 2009a; RCOG, 2009; Mc Donald, 2008; Van Rheen, 2007; Hutton, 2007; Chaparro, 2006; Ceriani et al, 2006; Rabe, 2004). Blinding will also be done by administration of 1 ml of normal saline to mimic oxytocin injection.

#### **Control (COMPARISON) group**

The comparison group on the other hand will involve the standard/ gold procedure in the management of third stage of labor. Mothers will be given oxytocin 10 IU as the prophylactic uterotonic agent within one minute following delivery of the baby. This time according to Tharakan and Jha (2008) is more effective and safe compared to injection after delivery of placenta. This group will also receive a placebo taken sublingually to blind for misoprostol. This group will be the control group. Delayed cord clamping will also be preferred.

In all the two groups, the placenta will be delivered manually if not delivered after 30 minutes. In case bleeding persists, additional uterotonic agents, bladder emptying, expulsion of clots, blood transfusion or surgical procedures like hysterectomy will be used to manage PPH and this will be documented for all the groups.

Same sublingual route of administration will be preferred due to its pharmacodynamics properties including; rapid onset of action, greater bioavailability

[figure not shown]

and prolonged activity (Tang et al, 2002; Andolina, 2003; Hofmeyr, 2005; Khan, 2003; Abdel-Aleem, 2003). Similar misoprostol doses will also be maintained to avoid variations in plasma therapeutic levels (Mousa and Alfrevic, 2009, Tang et al, 2002). Single doses of recommended 600µg misoprostol will be used as opposed to repeated doses (FIGO/ICM, 2006).

**A.5.4 Please justify your choice of sample size (as described in A.4)**

The two main research questions guiding this particular trial were to assess whether sublingual 600µg misoprostol, with an advantage of not requiring skilled administration and special storage was no worse (non-inferior) than 10 IU oxytocin in prevention of PPH. The trial is also to assess whether sublingual misoprostol 600µg is reasonably efficacious and a feasible alternative to oxytocin in the active management of thirds stage of labor especially in resource-limited settings. The primary outcome of this trial will be maternal blood loss  $\geq 500$  mL within 24 hours postpartum.

In a superiority trial, one's null hypothesis is that the two groups are equal and your alternative hypothesis (or your main hypothesis) would be that one intervention is better (superior) than the other, in this case oxytocin (clinically/ technically, oxytocin has been preferred to misoprostol). In an equivalence trial (also known as a two-sided non-inferiority trial), your null hypothesis is that one arm is better than the other, and your alternative hypothesis is that they are equal. In a non-inferiority trial, your null is that one arm is better than the other and your alternative hypothesis is that the alternative intervention (with particular advantages- misoprostol) is not worse or non-inferior to the standard (oxytocin). A pre-defined margin of non-inferiority ( $\Delta$ ) has to be stated since it is almost impossible to prove exact equality (Gulmezoglu et al, 2009; Piaggio et al, 2009; Lesaffre, 2007). This  $\Delta$  defines the upper bound ( $\Delta_{NI}$ ) and alternative treatment will be considered non-inferior to the standard if the 95% CI  $\Delta$  lies left of  $\Delta_{NI}$ . Unlike in the superiority trials, non-inferiority trials are unpopular reported using p-values but (two-sided) 95% CI (Lesaffre, 2007). Non-inferiority trial therefore requires rejection of a null hypothesis ( $H_0: \Delta > \Delta_{NI}$ ) and prove the alternative ( $H_1: \Delta < \Delta_{NI}$ ). Alternatively,  $p < 0.025$  is considered as significant to prove that the alternative treatment is not worse/ non-inferior based on predefined  $\Delta_{NI}$  (D'Agostino et al, 2006).

[figure not shown]

To determine the inferiority margin ( $\Delta_{NI}$ ), the effect of standard treatment (oxytocin) was compared and its benefit over intervention treatment (misoprostol) in prevention of PPH ( $\geq 500$  mls). Several Cochrane reviews and well designed trials that had blood loss as an outcome were considered. A 6% difference in blood loss of  $\geq 500$  mls was therefore considered to be confident that misoprostol is a reasonable alternative to oxytocin and of vital benefit compared to no intervention. This is within the percent window of  $\pm 10\%$  to be confident that misoprostol can be superior, inferior, non-inferior or equal to oxytocin.

For studies intending to test a non-inferiority hypothesis, the recommended equation for sample size determination (WHO, 2010; Feinstein, 2002; Fleiss, 1980)

$$n \text{ (for each group)} = \frac{2 \times [sd]^2}{\delta^2} \times (Z_{\alpha} + Z_{\beta})^2$$

For a test of proportions, the  $sd = \sqrt{p_1q_1 + p_2q_2}$  (where  $p_1$  = probability in standard group and  $p_2$  = probability in intervention group.  $Q=1-p$ )

$$n = \frac{2 \times [p_1(1-p_1) + p_2(1-p_2)]}{\delta^2} \times (Z_{\alpha} + Z_{\beta})^2$$

Prophylactic oxytocin (standard treatment) reduces the rate of blood loss  $> 500$  mls by 50% compared to no uterotonics at all/ placebo (RR 0.50, 95% CI 0.43 to 0.59) (Cotter et al, 2007, Elbourne et al, 2001; Prednville et al, 2001)

Oral misoprostol significantly reduces the rate of acute PPH ( $>500$  mls of blood loss) by 47% compared to placebo (RR 0.53, 95% CI 0.39-0.74,  $p < .0001$ ) (Derman et al, 2006)

A multi-site study significantly documented proportions of 20% for PPH in the misoprostol arm compared to 14% in the oxytocin arm for post-partum hemorrhage ( $\geq 500$  mls) (Gulmezoglu et al, 2001)

$P_1 = 0.20$ ;  $P_2 = 0.14$

delta ( $\delta$ ) = 6% (0.06)

A level of confidence interval 95% (two sided) will be considered and therefore  $Z_{crit} = 1.96$

A statistical power of 90% will be considered for  $Z$

Given a predicted incidence of 14% PPH in mothers treated with prophylactic oxytocin and 28% for those who receive no intervention (placebo), a delta of 6% is within the limits

[figure not shown]

required to be confident that misoprostol is a reasonable alternative to oxytocin and of vital benefit compared to no intervention. A total of **1140** mothers will therefore be needed to achieve a 90% power (two sided) to say that misoprostol is no worse than oxytocin in PPH prevention. Each of the two groups, misoprostol and oxytocin will comprise of 570 mothers.

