## Hypothesis

Ho: 10 IU Oxytocin is significantly better than sublingual misoprostol 600µg in management of third stage of labor

H1: Sublingual misoprostol 600µg is non- inferior to 10 IU oxytocin and will not be more than 6% worse [than 10 IU oxytocin] in management of third stage of labor

[figure not shown]

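### The claimed 90% power with 570 women per arm does not follow from the protocol's inputs; under its own 95% CI rule the power is about 83% even if both arms have a 14% rate

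*Protocol*

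**What the plan says.** The Hypothesis section sets the margin: misoprostol "will not be more than 6% worse" than oxytocin. Section A.5.4 supports the margin by saying that a 6% difference in the primary outcome "was therefore considered to be confident that misoprostol is a reasonable alternative to oxytocin and of vital benefit compared to no intervention".

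The same section prints a formula that it recommends for non-inferiority studies: n per group = 2 × [p1(1 − p1) + p2(1 − p2)] / δ² × (Zα + Zβ)². It cites the prior evidence ("A multi-site study significantly documented proportions of 20% for PPH in the misoprostol arm compared to 14% in the oxytocin arm for post-partum hemorrhage") and then enters P1 = 0.20, P2 = 0.14 and δ = 0.06. On the level it says "A level of confidence interval 95% (two sided) will be considered", with a critical value of 1.96. Earlier in the section, p < 0.025 "is considered as significant to prove that the alternative treatment is not worse/ non-inferior based on predefined" margin. On power it says "A statistical power of 90% will be considered for" the second Z.

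The closing argument begins "Given a predicted incidence of 14% PPH in mothers treated with prophylactic oxytocin and 28% for those who receive no intervention" and continues that "a delta of 6% is within the limits" needed. It ends with 1140 women, 570 per arm, for 90% power to say that misoprostol is no worse. Section 3.4.3 (Data Reporting) bases the conclusion on where the two-sided 95% CI lies relative to the margin.

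**The concern.** A non-inferiority sample size needs two separate quantities: the margin and the true difference expected between the arms. Power depends on the gap between them. A.5.4 gives only the margin. The one pair of arm rates that it enters differs by 0.20 − 0.14 = 0.06, so the gap between margin and difference would be zero if those were the expected rates. If equal rates were intended instead, the text does not say so, and it is unclear why unequal rates were entered.

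The central power statement therefore has no visible basis. Investigators, ethics reviewers and the safety board would read 90% as the chance of a conclusive result when misoprostol is no worse. If the real figure is lower and drops quickly with a small true disadvantage, an inconclusive result is more likely than the protocol leads them to expect.

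**Working it through.** **Inputs, all from the protocol.** Rates 0.20 (misoprostol) and 0.14 (oxytocin); δ = margin = 0.06; Z = 1.96 (one-sided 0.025); power 90%, so Z = 1.2816; 570 per arm, 1:1. No dropout allowance is stated and none is used.

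**1. Trying to reproduce 570 from the listed inputs.**
- Variance sum: 0.20 × 0.80 + 0.14 × 0.86 = 0.1600 + 0.1204 = 0.2804.
- (1.96 + 1.2816)² = 10.508.
- Printed formula: 2 × 0.2804 / 0.0036 × 10.508 ≈ 1637 per group.
- Without the factor 2 (the bracket already sums both arms' variances): 0.2804 / 0.0036 × 10.508 ≈ 818 per group.
- A conventional superiority comparison of 20% with 14% (Fleiss, two-sided 5%, 90% power): 822 per group, or 855 with continuity correction.

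None of these is near 570.

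**2. What does match 570.** With 14% in both arms, n = 2 × 0.1204 / 0.0036 × (Zα + Zβ)² = 66.89 × (Zα + Zβ)².
- One-sided 5%: 66.89 × (1.645 + 1.2816)² gives 573. With Z values rounded to 1.64 and 1.28, 66.89 × 2.92² = 570.3.
- One-sided 2.5%: 66.89 × 10.508 gives 703.

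A search over equal rates of 12% to 18% and 20%, at one-sided 2.5% and 5%, found only one match within 3% of 570 at the stated 90% power: 14% with one-sided 5%. Other near matches need a different power (for example 13%, one-sided 2.5%, 85% power: 565). The protocol does not show this step, so the match is an inference.

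**3. Power with 570 per arm under the stated 95% CI rule.** Power = Φ((0.06 − d)/SE − 1.96), with SE = √{[pM(1 − pM) + 0.14 × 0.86]/570} and pM = 0.14 + d.

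At d = 0: SE = √(0.2408/570) = 0.02055; 0.06/0.02055 − 1.96 = 0.96; power 83.1% (simulation 83.2%).

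| True difference d (points) | Misoprostol rate | Power |
|---|---|---|
| 0 | 14% | 83% |
| +1 | 15% | 67% |
| +2 | 16% | 47% |
| +3 | 17% | 29% |
| +4 | 18% | 15% |
| +6 | 20% | 2.5% |

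At 14% the CI half-width is 1.96 × 0.02055 = 4.0 points, so non-inferiority needs an observed difference below about 6.0 − 4.0 = 2.0 points. At one-sided 5% the power at d = 0 would be 89.9%, which is where the 90% appears to come from.

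**4. Labels.** A.5.4 defines p1 as the standard group and p2 as the intervention group, then gives p1 the misoprostol rate. The variance sum is symmetric, so n is unaffected. The sentence on the cited study fixes the direction.

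**The case against.** The best defence is that 20% versus 14% was never a forecast for this trial. A.5.4 reports it as an earlier study's result. The only rates that it calls predicted are 14% on oxytocin and 28% without intervention, and the Summary (A.2) expects the sublingual route to improve on the oral one. The formula uses the rates only in the variance and divides by the squared margin, which is the ordinary non-inferiority form when the true difference is zero. On that reading the design is sensible, and 83% power is respectable.

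Much of this stands, and it rules out two stronger readings. A reader might infer that the trial has 2.5% power under its own planning assumption and so fails by design. The protocol does not support this: it nowhere says that it expects 20% on sublingual misoprostol. If misoprostol really were 6 points worse, declining to conclude non-inferiority would be the correct result, and 2.5% is simply the type I error at the margin. A reader might also infer that the calculation is a superiority comparison of 20% with 14% under a non-inferiority label. Step 1 shows that this does not produce 570 either, whereas an equal-rates non-inferiority calculation at a looser level does.

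The defence does not rescue the power statement. Equality of rates is nowhere stated, the listed inputs do not give the stated number, and the level that does give it contradicts the level stated in the text.

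**Conclusion.** The point holds in this form: the claim of 90% power with 570 per arm is wrong as written. The listed inputs lead to about 1637 or 818 per group. The matching calculation uses an unstated equal rate of 14% and an unstated one-sided 5% level, against the two-sided 95% CI, Z = 1.96 and p < 0.025 in A.5.4 and the 95% CI rule in section 3.4.3. Under the stated rule the power is about 83% at best among the non-negative true differences examined, and below one half once misoprostol is truly 2 points worse. The 2.5% applies only if the entered rates are the true ones.

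These figures assume a 14% oxytocin rate, the normal approximation with unpooled variance, and complete data on 570 women per arm. That 570 came from equal rates at one-sided 5% is inferred from the numerical match; the discrepancy with the stated inputs does not depend on that inference. The swapped labels are a clerical error.

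**What to change.** Rewrite the sample-size paragraphs of A.5.4 as follows.

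- Separate the 6-point margin from the assumed true difference, and state the latter: 14% in both arms, difference zero.
- Describe 20% versus 14% as evidence for the margin, not as planning rates.
- Correct the formula and inputs so that they lead to the stated number at one-sided 0.025, matching the two-sided 95% CI.
- Withdraw the 90% claim and replace it with about 83% at 570 per arm. Note that 90% would need about 703 per arm (1406 in total, 1406 − 1140 = 266 more women).
- Add the power at true differences of 0, +1, +2, +3 and +6 points.
- Correct the p1 and p2 labels; this does not change the number.

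The cost is protocol wording and a short table. Enrolment need not change if the sponsor accepts 83%; the downside is a less favourable stated power. Making the text consistent by moving to a one-sided 5% level would restore about 90%, but only by loosening the decision rule that the protocol sets out in A.5.4 and section 3.4.3.

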### 3.4.3 Data Reporting

Results will be analyzed and presented as per the current CONSORT guidelines (Piaggio et al, 2006). The proportions will be presented as percentages and their confidence Intervals will be presented at 95% (two-tailed) at the power of 95%. Two-tailed statistical analysis will be used and statistical significance will be defined at level of  $p \leq 0.05$ . If the lower limit of the 95% confidence interval lies to the right of the non-inferiority margin ( $\Delta$ ) the experimental intervention will be regarded "**inferior**". If results lie left of  $\Delta$ , it will be concluded as **non-inferior** with regard to that pre-stated margin  $\Delta$ . If the results are inconclusive regarding the non-inferiority hypothesis and the whole 95% confidence interval lies to the right of zero, it will be concluded that the misoprostol is **significantly worse** according to a superiority hypothesis.

[figure not shown]

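### The 90% power claimed for 1140 mothers does not follow from the protocol's own inputs; under its two-sided 95% interval, 570 per arm gives about 83% if both true rates are 14%

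*Protocol*

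**What the plan says.** Section A.5.4 of the Protocol fixes every element of the calculation.

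- **Level:** "A level of confidence interval 95% (two sided) will be considered and therefore" the critical value is 1.96. The same section gives the equivalent p-value rule: p < 0.025 "is considered as significant to prove that the alternative treatment is not worse/ non-inferior based on predefined" margin.
- **Power:** "A statistical power of 90% will be considered for" the second Z term.
- **Margin:** delta = 0.06. The Hypothesis section agrees: misoprostol "will not be more than 6% worse" than oxytocin.
- **Rates:** P1 = 0.20 and P2 = 0.14, from a multi-site study that "documented proportions of 20% for PPH in the misoprostol arm compared to 14% in the oxytocin arm". The text then predicts 14% on oxytocin and 28% with no treatment. It also cites a relative risk of 0.53 for oral misoprostol against placebo.
- **Formula, per group:** n = 2 × [p1(1−p1) + p2(1−p2)] / δ² × (Zα + Zβ)².
- **Result:** 1140 "mothers will therefore be needed to achieve a 90% power (two sided) to say that misoprostol is no worse than oxytocin in PPH prevention", 570 per group.

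Section 3.4.3 (Data Reporting) judges the result by the position of the two-sided 95% interval relative to the margin, for example "If the lower limit of the 95% confidence interval lies to the right of the non-inferiority margin". It also says that "confidence Intervals will be presented at 95% (two-tailed) at the power of 95" per cent.

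**The concern.** The sample size is presented as the consequence of the inputs listed just above it, yet a reader who enters those inputs does not obtain it. If the number rests on a looser significance level than the one used for the decision, the trial's chance of demonstrating non-inferiority is lower than stated. Section 3.4.3 expressly allows for an inconclusive result, and such a result would be read as coming from a 90%-power trial. The mismatch also leaves room for someone to argue after the data are in that a 90% interval was intended, by pointing to the basis of the sample size.

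**Working it through.** **Inputs** (all from A.5.4 unless noted): rates 0.20 and 0.14; δ = 0.06, so δ² = 0.0036; Zα = 1.96; 90% power, so Zβ = 1.2816; (1.96 + 1.2816)² = 10.508. Binomial variances: 0.20 × 0.80 = 0.1600 and 0.14 × 0.86 = 0.1204.

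**Step 1. Attempt to reproduce 570 per arm.**

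| Calculation | Arithmetic | Per arm | Total |
|---|---|---|---|
| Formula and inputs as printed | 2 × 0.2804 / 0.0036 × 10.508 | 1,637 | 3,274 |
| Same, without the extra factor 2 | 0.2804 / 0.0036 × 10.508 | 819 | 1,638 |
| Non-inferiority, 14% in both arms, Z = 1.96 | 0.2408 / 0.0036 × 10.508 | 703 | 1,406 |
| Non-inferiority, 14% in both arms, Z = 1.645 | 0.2408 / 0.0036 × 8.564 | 573 | 1,146 |

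The extra 2 is an error. The leading 2 belongs with a common per-arm variance. The protocol defines sd² as p1q1 + p2q2, which already sums the two arms, so multiplying by 2 counts them twice. The labels are also swapped: the text defines p1 as the standard group but then sets P1 to the misoprostol rate. The sum is unaffected by this.

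Of the variants tried at 90% power, only the last row comes close to 570. It is a likely origin, but an inferred one: the protocol never prints Z = 1.645, nor a 14% assumption for misoprostol. That level corresponds to a two-sided 90% interval and conflicts with Z = 1.96, p < 0.025 and the 95% interval rule.

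**Step 2. Power of 570 per arm under the stated rule.** Power = Φ[(0.06 − (pM − pO)) / SE − 1.96], with SE = √{[pM(1−pM) + pO(1−pO)] / 570}, where M is misoprostol and O is oxytocin.

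For 14% in both arms: SE = √(0.2408/570) = 0.02055; 0.06/0.02055 = 2.919; 2.919 − 1.96 = 0.959; Φ = 0.831. An exact binomial enumeration of the Wald interval rule gives 83.1%, and a Farrington-Manning variance gives 82.5%. With 1.645 in place of 1.96, the same formula gives 89.9%.

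| True rate, misoprostol / oxytocin | Source of the rates | Power |
|---|---|---|
| 14% / 14% | predicted oxytocin rate, no true difference | 83% |
| 17% / 17% | midpoint of 14% and 20% | 77% |
| 20% / 20% | entered misoprostol rate in both arms | 72% |
| 14.8% / 14% | 0.53 × 28% = 14.8% on misoprostol | 71% |
| 20% / 14% | the rates as entered | 2.5% |

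For the fourth row: SE = 0.02080; (0.06 − 0.008)/0.02080 = 2.50; 2.50 − 1.96 = 0.54; Φ = 0.71. In the last row the true difference equals the margin, so the numerator is zero and Φ(−1.96) = 0.025.

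**Step 3. What would give 90% at 570 per arm with the 95% interval.** A common rate of 11% gives 89.9%. Misoprostol at 13% against oxytocin at 14% gives 93.3%. The protocol assumes neither.

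**The case against.** Three arguments deserve weight.

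First, 83% is not a ceiling. A reader might infer that 570 per arm can reach 83% at best, or that 90% is attainable only with a one-sided 5% test. The documents do not support either statement: power under the 95% interval is about 90% at 11% in both arms and higher if misoprostol is truly better. This stands, so the 83% must be given as conditional on 14% in both arms. It does not rescue the stated 90%, because the protocol predicts 14% on oxytocin and nowhere assumes an advantage for misoprostol.

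Second, 14% on misoprostol is itself an assumption supplied for this check. The protocol enters 20%, and its relative risk implies about 14.8%. This also stands, and it is why the unequal cases are shown. Both give lower power than 83%.

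Third, the two-sided 95% interval protects the type I error whatever power is quoted, so a positive non-inferiority conclusion is unaffected. That is correct. The harm is confined to the planning claim and to how an inconclusive result is read.

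Leaving detail to a separate analysis plan is no answer here, because the protocol itself fixes the inputs, the decision rule and the result.

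**Conclusion.** The point holds. The stated 90% power for 1140 mothers follows neither from the printed formula (1,637 per arm, or 819 once the duplicated factor is removed) nor from the standard non-inferiority calculation at the stated level (703 per arm). Under the protocol's own decision rule, 570 per arm gives about 83% power if both true rates are 14%. The chance of missing non-inferiority is then 17%, not 10%. Power is 71% to 77% under the other equal or nearly equal rates examined, and 2.5% if the entered 20% and 14% are the true rates. The 95% in section 3.4.3 is a second power figure that conflicts with the 90% in A.5.4.

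These figures assume 570 analysed mothers per arm with no losses, a 6-point absolute margin and a normal-approximation interval. That 570 came from a one-sided 5% level is a plausible reconstruction, not something the protocol states.

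**What to change.** In A.5.4:

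- Remove the duplicated factor 2 from the formula.
- Replace P1 = 0.20 and P2 = 0.14 as the assumed rates with an explicit assumption of 14% in both arms. Keep the 20% and 14% figures only as background to the margin.
- State the margin as 6 percentage points and the level as one-sided 0.025, equivalent to the two-sided 95% interval.
- Restate the power of 570 per arm as about 83% under that assumption, and show the lower figures for less favourable rates.

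In 3.4.3, keep the two-sided 95% interval rule and delete the reference to 95% power.

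This costs only protocol wording and a less favourable stated power; enrolment, margin and decision rule are unchanged. If the sponsor wants a true 90% at 14% in both arms, 703 per arm (1,406 in total) would be needed before any losses. That choice is the sponsor's.
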